### **Research sample taking**

A total of 5 venous blood samples will be collected from each participant, 1 as part of their standard clinical care, and 4 for study investigations. Each time, a qualified nurse will collect around 5ml (1 teaspoon) of blood. Serum from study blood samples will be extracted and stored in a secure research -80C freezer in OCMR for all participants. At the end of the study, study serum samples will be transported to the [name] Lab at the Department of Physiology, Anatomy and Genetics (DPAG), Part of the Medical Sciences Division of the University of Oxford for further investigational assays.

**Investigational assays** - Serum samples derived from all participants and all timepoints will be tested together. Tests include measurements of serum iron indices (iron, ferritin, transferrin and transferrin saturation) using automated analytical Chemistry instrument (Pentra C400) in the [name] Lab. Markers of tissue iron damage (HNE and MDA) will also be measured in serum samples using standard commercially available kits (Abcam ab118970 and ab238538 respectively).

## **9.7. Day1 - Baseline Assessments**

Example Study MRI schedule: Cohort 1 (3 participants per cohort)\*

| Day 1 - Baseline & 3h post IV iron infusion                                                                                                                                                                                                                                                                                           | 2 weeks (14+/-2days) - post IV iron infusion                                                                           | 6 weeks (42+/-2days) - post IV iron infusion                                                                           |
|---------------------------------------------------------------------------------------------------------------------------------------------------------------------------------------------------------------------------------------------------------------------------------------------------------------------------------------|------------------------------------------------------------------------------------------------------------------------|------------------------------------------------------------------------------------------------------------------------|
| 9:00 am - Participant #1 baseline (3 hrs)
12:00 pm - Participant #2 baseline (1 hr)
1:00 pm - Participant #3 baseline (1 hr)
2:00 pm – BREAK

3:00 pm – Participant#1 at 3hr-post iron (1 hr)
4:00 pm – Participant #2 at 3hr-post iron (1 hr)
5:00 pm - Participant #3 at 3hr-post iron (1 hr)
6:00 pm – END | 9:00 am - Participant #1 (1hr)
10:00 am - Participant #2 (1hr)
11:00 am - Participant #3 (1hr)
12:00 pm - END | 9:00 am - Participant #1 (1hr)
10:00 am - Participant #2 (1hr)
11:00 am - Participant #3 (1hr)
12:00 pm - END |

\* Repeat for Cohort 2 and Cohort 3, Cohort4.

Baseline clinical data for each Participant:

- Confirmation against inclusion and exclusion criteria

Baseline MRI scan (for Participant #1 in each cohort; up to 3 hours)

- Cine imaging for cardiac structure and function
- Tissue characterisation by R1/R2/R2\* relaxometry of the heart, liver, spleen, blood and skeletal muscle over 3 hours.

Baseline MRI scan (for Participant #2 and #3 in each cohort; up to 1 hour)

- Cine imaging for cardiac structure and function
- Tissue characterisation by R1/R2/R2\* relaxometry of the heart, liver, spleen, blood and skeletal muscle over 1 hour.

Baseline laboratory data:

- In addition the research team member will collect participant's demographic information and medical history from their medical notes.
- Haemoglobin, iron, transferrin saturation and ferritin data available from medical notes.

Baseline blood samples:

- Two collected, one as part of standard clinical care, and the other for study investigations to measure serum iron indices and serum markers of tissue iron damage.

Intravenous iron infusion:

- Administered by a member of the clinical care team as part of standard clinical care

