| Secondary       | Determine the effects of iron infusion (Ferric carboxymaltose, Ferinject, 1000mg) on serum iron indices and serum markers of tissue iron damage. | Change from baseline in:
1. Serum iron indices: iron, ferritin, transferrin saturation, non-transferrin bound iron
2. Serum markers of tissue iron damage, including but not limited to lipid peroxidation markers malondialdehyde (MDA) and 4-Hydroxynonenal (HNE) | Baseline, prior to infusion (day 1)
Timepoint 1- 3hr post infusion (day 1)
Timepoint 2- ~2 weeks post infusion
Timepoint 3- ~6 weeks post infusion |
| Intervention(s) | None- This is a non-interventional observational study                                                                                           |                                                                                                                                                                                                                                                                           |                                                                                                                                                             |
| Comparator      | None                                                                                                                                             |                                                                                                                                                                                                                                                                           |                                                                                                                                                             |

\* - refers to a parameter derived from raw MRI data

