**23. APPENDIX B: SCHEDULE OF STUDY PROCEDURES**

| Procedures             | Screening  | Baseline (OCMR)                     | Timepoint 1 (OCMR)                    | Timepoint 2 (OCMR)                         | Time point 3 (OCMR)                        |
|------------------------|------------|-------------------------------------|---------------------------------------|--------------------------------------------|--------------------------------------------|
|                        |            | Day 1 - prior to Ferinject infusion | Day 1- 3hours post Ferinject infusion | Day 14 (+/- 2days) post Ferinject infusion | Day 42 (+/- 2 days post Ferinject infusion |
| Eligibility check      | X          |                                     |                                       |                                            |                                            |
| Informed consent       | X (verbal) | X                                   |                                       |                                            |                                            |
| Demographics           |            | X                                   |                                       |                                            |                                            |
| Medical history        |            | X                                   |                                       |                                            |                                            |
| Research blood samples |            | X                                   | X                                     | X                                          | X                                          |
| Clinical data          |            | X                                   |                                       |                                            |                                            |
| MRI scan               |            | X                                   | X                                     | X                                          | X                                          |

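### The example day-1 timetable starts each 3-hour scan exactly 180 minutes after the baseline slot ends, so full-length baseline slots leave no time for the infusion

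*Protocol*

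**What the plan says.** The Synopsis lists the early measurement as "Timepoint 1- 3hr post infusion (day 1"), and Section 6 repeats this. Appendix B heads the column "Day 1- 3hours post Ferinject infusion" and places the baseline assessments before the infusion on the same day.

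Section 9.7 gives an example MRI timetable for Cohort 1, to be repeated for Cohorts 2 to 4. Section 9.6.2 points to Section 9.7 and Appendix D for how the cohorts will be run. Taken person by person, with a break between the morning and afternoon blocks, the slots are:

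- The first person scanned has the extended baseline slot, "9:00 am - Participant #1 baseline (3 hrs"), and returns in the afternoon for "3:00 pm – Participant#1 at 3hr-post iron (1 hr").
- The second person has a standard baseline slot, "12:00 pm - Participant #2 baseline (1 hr"), and returns for "4:00 pm – Participant #2 at 3hr-post iron (1 hr").
- The third person also has a standard baseline slot, "1:00 pm - Participant #3 baseline (1 hr"), and returns last, for "5:00 pm - Participant #3 at 3hr-post iron (1 hr").

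The timetable has no line for the infusion. The protocol text gives no infusion duration and does not say whether the 3 hours run from the start or the end of the infusion. The 2-week and 6-week visits each have a tolerance of 2 days either way; the 3-hour visit has none.

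**The concern.** The infusion has to fall between the baseline scan and the second scan. If the whole interval between those scans is 3 hours, the second scan cannot also start 3 hours after the infusion has finished. The identical gaps suggest that the 3 hours were counted from the end of the baseline scan rather than from the infusion.

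The primary objective is the kinetics of iron uptake, and Section 5 looks to the early timepoints for evidence of rapid, unregulated uptake. The 3-hour scan is the only post-infusion measurement before week 2. Section 11.1 plans exploratory pharmacodynamic modelling, and Section 11.4 plans an interim look after the first cohort at whether the timepoints are appropriate. Both need to know when the early scan was really taken. Section 11 says there is no separate analysis plan, so the protocol is where this would be settled.

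**Working it through.** **Inputs.** Slot start times and lengths come from the Section 9.7 timetable. The order (baseline, infusion, second scan) comes from Appendix B.

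**Step 1: gap between scans.** Gap = second scan start − (baseline start + baseline slot length).

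| Participant | Baseline slot | Second scan starts | Gap |
|---|---|---|---|
| 1 | 09:00 + 3 h = 12:00 | 15:00 | 180 min |
| 2 | 12:00 + 1 h = 13:00 | 16:00 | 180 min |
| 3 | 13:00 + 1 h = 14:00 | 17:00 | 180 min |

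The labelled 3 hours is therefore the interval from the end of the baseline slot to the next scan.

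**Step 2: time since infusion at scan start.** Let *t* be the turnaround from scanner to start of infusion, *i* the infusion time, and *d* = *t* + *i*.

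- Counted from the end of infusion: 180 − *d* minutes. This equals 180 only if *d* = 0.
- Counted from the start of infusion: 180 − *t* minutes. This equals 180 only if *t* = 0.

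**Step 3: size.** The protocol gives neither *t* nor *i*, so *d* is an assumed range. Counted from the end of infusion, the 1-hour slot runs from 180 − *d* to 240 − *d* minutes, with its midpoint at 210 − *d*.

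| Assumed *d* (min) | Slot starts (min) | Shortfall at start | Slot midpoint (min) | Slot ends (min) |
|---|---|---|---|---|
| 15 | 165 | 15/180 = 8.3% | 195 | 225 |
| 30 | 150 | 30/180 = 16.7% | 180 | 210 |
| 45 | 135 | 45/180 = 25.0% | 165 | 195 |
| 60 | 120 | 60/180 = 33.3% | 150 | 180 |

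For 0 < *d* < 60 the slot begins before 180 minutes and ends after it, so acquisition straddles 3 hours.

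**Step 4: if baseline finishes early.** Section 9.7 gives scan lengths as upper limits. If Participant 1's extended scan ended at 11:30, the gap would be 15:00 − 11:30 = 3.5 hours, enough for *d* up to 30 minutes.

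**The case against.** The timetable is labelled an example and covers scanner slots only, so the absence of an infusion line is not in itself an error. The slot lengths are maxima, and early finishes would create room. Time zero is not named; counted from the start of infusion, only the turnaround is lost. Appendix D and the flow chart are figures that are not shown, and the case report form is not at hand, so infusion timing may be specified or recorded there. The main outcome is change from baseline at each nominal timepoint, and modelling is exploratory. With the next visits at 14 and 42 days, tens of minutes barely move the time axis, and the interim look after the first cohort gives a chance to correct the schedule.

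Much of this stands and limits the point. It does not remove it. Section 9.6.2 names this timetable as showing how cohorts will be run; the slots are back to back, and no slack is planned. An early finish would lengthen the interval by an amount the protocol text does not ask anyone to record.

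A reader might go further in four ways that the protocol does not support:

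- **No time for the blood draw.** The order of the baseline sample and the scan is not stated; the sample could come first.
- **Early data always taken before 3 hours.** Only the scan start falls short, and only with full baseline slots; the acquisition straddles 3 hours for any delay under 60 minutes.
- **A shortfall that varies between participants.** The three timetabled gaps are identical.
- **A spread in imaging time between organs.** This applies to any hour-long scan, including baseline, and does not come from the timetable.

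**Conclusion.** The example timetable and the 3-hour definition conflict when baseline slots are fully used. A scan cannot then start a full 3 hours after the end of infusion, and it starts 3 hours after the beginning of infusion only with zero turnaround. The 180-minute gaps follow directly from the document. The size of the shortfall does not: the starts at 165, 150 and 120 minutes rest on assumed delays of 15, 30 and 60 minutes.

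The consequence is confined to the time label of the early point and the exploratory kinetic and pharmacodynamic modelling. A reader might infer that power or the detection of an acute rise is compromised. The protocol does not support that: the sample of 12 was not derived statistically (Section 11.2), and a scan somewhat earlier than 3 hours still addresses whether tissue iron rises acutely. The point merits correction because it concerns a stated figure for the only post-infusion measurement before week 2.

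**What to change.** Reconcile the Section 9.7 timetable with the 3-hour definition in Sections 3 and 6 and Appendix B, in one of two ways:

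- move the three afternoon slots later by the turnaround plus infusion time (by the turnaround alone if time zero is the start of infusion); or
- restate timepoint 1 as the interval actually delivered.

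In either case, name time zero as the start or the end of infusion, and give the timepoint a window in minutes. Record infusion start, infusion stop and scan start times, and use actual elapsed minutes in the kinetic and pharmacodynamic analyses.

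The cost is small. Moving the slots ends the scanner day later by the same amount: for an assumed 15, 30 or 45 minutes, at 18:15, 18:30 or 18:45 instead of 18:00. Restating the timepoint costs one reworded definition, carried through the sections above. Either way a few recorded times are added, and the infusion itself is unaffected.

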**Key question with safety implications**- We do not know how I.V iron formulations affect myocardial iron levels and cardiac function in the long term. Answering these questions is important for ensuring that correction of iron deficiency is not accompanied by myocardial iron toxicity. It is widely assumed that I.V iron formulations such as Ferinject (ferric carboxymaltose or FCM) are taken up and degraded by macrophages, allowing slow and controlled release of iron into the circulation, and subsequent loading onto the plasma iron chaperone transferrin for uptake by tissues. Most tissues can prevent excess iron accumulation by downregulating the levels of transferrin receptor expression (this is achieved through the iron-sensing function of iron-regulatory proteins IRPs). However, kinetic studies of plasma iron indices, together with the speed of manifestation of associated physiological effects demonstrate that FCM infusion results in rapid and physiologically-relevant rise in non-transferrin bound iron (NTBI) in the plasma. Excess NTBI in the plasma is dangerous because it is taken up by tissues through L-type and T-type calcium channels, which are not regulated by IRPs. These channels are highly expressed in the heart and it is well established that they are responsible for the iron overload cardiomyopathy that occurs in genetic disorders of iron overload such as hemochromatosis (where NTBI is also raised). In pre-clinical mouse models, we found that a patient-equivalent dose of intravenous iron resulted in ~400% increase in cardiac iron levels.

**Study rationale** - This is a pump-priming study to establish if the standard intravenous iron treatment, given as part of standard clinical care to correct iron deficiency, results in an acute rise in tissue iron levels, including myocardial iron at the early timepoints, which would be evidence for the direct, rapid unregulated route of iron uptake. It is an observational cohort study measuring changes in tissue iron levels from baseline following infusion of intravenous iron. Tissue iron levels will naturally vary between individuals. Because of this, the study will not use a placebo arm. Instead, it will measure changes against baseline tissue iron levels.

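### In 8 of 12 participants the section 9.7 timetable starts the 2-week and 6-week scans two hours earlier in the day than the baseline scan, an avoidable one-directional shift that no control arm can remove

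*Protocol*

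**What the plan says.** Section 9.7 of the Protocol sets out a three-column MRI timetable for Cohort 1, headed as an example, with a note to repeat it for Cohorts 2 to 4. Section 9.6.2 groups participants into 4 cohorts of 3 and refers to section 9.7 and Appendix D for how cohorts are run.

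On day 1, participant #1 has an extended 3-hour baseline scan from 9:00, and the other two follow: "12:00 pm - Participant #2 baseline (1 hr) 1:00 pm - Participant #3 baseline (1 hr) 2:00 pm – BREAK". The 3-hour post-infusion scans start at 15:00, 16:00 and 17:00. At 2 weeks and again at 6 weeks, participant #1 is scanned at 9:00 and the others as "10:00 am - Participant #2 (1hr) 11:00 am - Participant #3 (1hr) 12:00 pm - END".

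There is no placebo arm. The rationale in section 5 states: "Instead, it will measure changes against baseline tissue iron levels". Section 11.1 defines the primary outcome as the absolute change from baseline in R1, R2 and R2* at each timepoint. Section 11.6 sets a two-sided 0.05 level. The visible text contains no rule that follow-up should match the baseline time of day, no clock time for any study blood sample, and no instruction on food or fluid.

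**The concern.** When the only comparator is a person's own baseline, the baseline and follow-up measurements should differ in time since infusion and in as little else as possible. For slots #2 and #3 the timetable adds a second, systematic difference. Both follow-ups start two hours earlier in the day than baseline, in the same direction for every affected participant. Such a shift does not average out over participants, and there is no concurrent group from which to subtract it.

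The shift is also tied to slot. Slot #1 keeps its start time but has the longer baseline scan, so a difference between slot #1 and the other two slots would be hard to interpret.

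At stake is the reading of the week-2 and week-6 changes. If relaxometry or serum measures vary over the late morning and midday, part of an observed change could reflect the clock. This matters most where the true change is small.

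**Working it through.** **Inputs.** Start times and scan lengths come from the section 9.7 timetable, the 4 cohorts of 3 from section 9.6.2, the outcome definition from section 11.1 and the 0.05 two-sided level from section 11.6.

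**Plan's own figure.** 4 × 3 = 12, which agrees with the synopsis and section 11.2. Section 11.2 says the number was not derived statistically, so there is no power figure to reproduce.

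**Clock-time shift = visit start − baseline start.**

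| Slot | Baseline | 3-hour scan | Weeks 2 and 6 | Shift at 3 h | Shift at weeks 2 and 6 |
|---|---|---|---|---|---|
| #1 | 9:00 (3 h long) | 15:00 | 9:00 | +6 h | 0 h |
| #2 | 12:00 | 16:00 | 10:00 | +4 h | −2 h |
| #3 | 13:00 | 17:00 | 11:00 | +4 h | −2 h |

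**Participants affected.** At weeks 2 and 6: 2 per cohort × 4 cohorts = 8 of 12 (67%), with a mean shift over all 12 of (0 − 2 − 2)/3 = −1.33 h. At the 3-hour scan: 12 of 12, with a mean shift of (6 + 4 + 4)/3 = +4.67 h.

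**Slot #1 by scan midpoint.** Baseline runs 9:00 to 12:00 (midpoint 10:30) and follow-up 9:00 to 10:00 (midpoint 9:30). The start times match, but the midpoints differ by 1 h.

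**Effect on the mean change.** Suppose the two-hour shift adds an offset d to the change in the 8 affected participants and nothing in the other 4. The bias in the mean is (8 × d + 4 × 0)/12 = 0.67d.

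**What d would do to a test.** The documents give no value for d, so it is varied as an assumption, in units of the standard deviation of the change. The figures come from 100,000 simulated studies with n = 12, no true iron effect and a two-sided one-sample t-test at 0.05. The t-test stands in for one timepoint's contrast with baseline; the protocol names ANOVA.

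| Assumed d (SD of change) | Bias in mean (SD) | False-positive rate |
|---|---|---|
| 0 | 0 | 5.0% |
| 0.1 | 0.07 | 5.5% |
| 0.25 | 0.17 | 8.0% |
| 0.5 | 0.33 | 16.9% |
| 0.75 | 0.50 | 30.7% |
| 1.0 | 0.67 | 47.1% |

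An offset of a tenth of a standard deviation is nearly harmless, while one of half a standard deviation is not. Nothing in the protocol says which row applies.

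**After the fix.** With each slot at its own baseline start time, the start-time shift at weeks 2 and 6 is 0 h in 12 of 12.

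**The case against.** The timetable is labelled an example and covers MRI slots only, so it shows what is intended without binding the site. Appendix A and Appendix D are figures not available here, and section 9.10 refers to a separate sample-handling procedure; any of these may address timing. This stands as a limit on how firmly the point can be put. Against it, section 9.6.2 points to section 9.7 for how cohorts are run, the note extends the timetable to every cohort, and no visible text overrides it.

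A reader might infer three stronger claims, and the documents support none of them.

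- *That serum iron changes are inflated by some percentage.* Blood-draw times are not given, no diurnal rate is stated, and serum indices are secondary. A percentage-per-hour figure would have no anchor and would say nothing about the primary relaxometry outcome.
- *That meals are mixed into the change.* No meal is mentioned. A participant scanned at 12:00 may well not have eaten lunch. The most that can be said is that food intake is not standardised in the visible text and that two baseline slots fall around midday.
- *That 8 of 12 describes every change from baseline.* It applies to weeks 2 and 6 only. At the 3-hour scan, which bears on the acute rise that the rationale emphasises, all 12 are shifted, and by more.

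It can also be said that this is a pump-priming study of 12 people, and that a large iron effect would swamp a modest clock effect. That is fair, and it keeps the point small. It does not justify leaving in place a shift that can be removed cheaply.

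**Conclusion.** The point holds as an inexpensive design improvement. As timetabled, the week-2 and week-6 changes in 8 of 12 participants carry a two-hour, same-direction shift in time of day, and the design has no means of separating it from the effect of iron. Bias from this is possible, not demonstrated. Its size is 0.67d for an unknown offset d, and neither the magnitude nor the direction of d can be taken from the documents. The conclusion assumes that the example timetable is followed in all four cohorts. For serum indices and damage markers it further assumes that blood is drawn near the scan. The larger shift of 4 to 6 h at the 3-hour scan is inherent in a same-day measurement. It is a limitation to report, not a fault to correct.

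**What to change.** In the section 9.7 timetable, start each 2-week and 6-week visit at the participant's own baseline time: #2 at 12:00 and #3 at 13:00. Participant #1 can stay at 9:00. Alternatively, #1 can move to 11:00, which lies inside that participant's 9:00 to 12:00 baseline window and gives one continuous block from 11:00 to 14:00. By scan midpoint the two options are equally close to baseline: 9:30 or 11:30 against 10:30, 1 h either way.

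State that study blood is drawn at the same point relative to the scan at baseline and at both follow-ups. Record scan start, draw time and time of last meal at every visit.

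Add a sentence to section 11 or the study report that the 3-hour scan falls 4 to 6 h later in the day than baseline in all 12 participants, so the acute change cannot be separated from time of day.

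Cost: a timetable edit and three recorded times per visit. Follow-up days end at 14:00 instead of 12:00. If #1 stays at 9:00, the scanner has a two-hour gap from 10:00 to 12:00; the documents do not say whether it could be used. The continuous block avoids that gap.
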